### Participants

Participants will be adults residing in the Autonomous Community of Aragon (Spain) who have been diagnosed with long COVID-19 and meet criteria for at least one comorbid emotional disorder. Recruitment will take place at Hospital Royo Villanova from Zaragoza, Spain. An online dissemination campaign will also be conducted through social medial and in collaboration with the Long COVID-19 association from Aragón. Eligibility criteria to participate in the study are reported in Table 1. Participants will not be involved in the design, conduct or reporting the trial.

**Table 1 pone.0342908.t001:** Inclusion and exclusion criteria to participate in the randomized controlled trial.

Inclusion criteria	Exclusion criteria
Residing in the Autonomous Community of Aragon (Spain). Being at least 18 years old. Understanding of Spanish. Being diagnosed with long COVID-19: documented SARS-CoV-2 infection and persistence of symptoms beyond 12 weeks after the acute infection. Symptoms of depression (ODSIS≥7) and/or anxiety (OASIS≥8). Meeting the criteria for an emotional disorder diagnosis. Having access to the Internet. Signing the informed consent.	Pre-existing emotional symptoms prior to the acute SARS-CoV-2 infection. Currently receiving psychological treatment. Having a diagnosis of severe mental disorder (e.g., personality disorder, bipolar disorder, etc.). Active suicidal ideation at the time of the assessment. Individuals on psychotropic medication must maintain their dosage throughout the study, unless medically contraindicated.

Using the G*Power software [23], and taking into account the two study conditions, the five assessment points (pre-treatment, post-treatment, and follow-ups at 3, 6, and 12 months), as well as the statistical models planned for data analysis, we calculated a total sample size of 74 participants, achieving a statistical power of 90%, an alpha level of 0.05, and an effect size of 0.30. Considering an anticipated dropout rate of 20%, the required sample size is estimated at 45 participants per condition (total sample size = 90 participants).

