After confirming the presence of at least one emotional disorder according to the Anxiety and Related Disorders Interview Schedule for DSM 5 (ADIS-5; [27]), participants will complete the online pre-treatment assessment protocol and will then be informed by email of their group assignment (either the experimental or the waiting list control group). Randomization to the experimental or group condition will be conducted by an independent researcher who will consult the pre-generated randomization sequence. The psychologist will also be informed of the assigned group to facilitate the management and organization of the UP-based experimental group intervention.

Participants in the experimental group will be required to complete an in-person additional assessment before they can begin the program. Accordingly, individuals assigned to the experimental group will meet in Zaragoza with a member of the research team to complete the neuropsychological and cognitive tests and to provide a hair sample for subsequent cortisol/cortisone analysis (secondary objective of this study). After these assessment point, participants will receive the UP-based psychological intervention in 12 online group sessions, each lasting 2 hours. Given that long COVID-19 patients often report cognitive difficulties [28] a break of approximately 10 minutes will be scheduled midway through each session. After the intervention, participants will complete the online post-treatment assessment protocol, which will include the measures administered at pre-treatment and a satisfaction questionnaire. Follow-up online assessments will also be conducted at three, six and twelve months after the intervention. At these time points, a group online session will be scheduled to monitor progress and reinforce the emotion regulation skills learned during the UP psychological program. At the three and twelve-month follow-up assessments, participants will repeat the in-person assessment to complete the neuropsychological and cognitive tests and to provide the hair samples for cortisol/cortisone analyses. Participants will receive email reminders for these appointments.

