### Data analysis

First, descriptive statistics of clinical psychological diagnosis, sociodemographic, and long COVID-19 symptoms will be explored to characterize the sample at baseline. Means and standard deviations for psychological measures (i.e., ODSIS, OASIS, etc.) at pre-treatment will also be calculated to provide a baseline description of our sample.

Second, the main effect of time, group and time x group interaction will be analyzed. Several linear mixed-effects models will be employed for each dependent variable to be analyzed (i.e., primary outcomes such as anxiety and depressive symptoms; secondary outcomes such as memory failures, emotional regulation difficulties, etc.). For each of these models, Time (within-subject variable; T1 vs. T2 vs. T3 vs. T4 vs. T5) and Experimental Group (between-subject variable; Experimental vs. Waitlist) will be included as fixed effects. Random slopes for participants will also be considered and included as random effects in the model. The models will have the following structure: [Dependent Variable ~ Time × Experimental Group + (1|Participant)].

In participants from the experimental group, descriptive analyses will also be conducted to assess their neuropsychological and cognitive status, as well as stress levels (hair cortisol and cortisone), prior to starting the intervention. Repeated measures ANOVAs with time as the within-subject factor will be performed to determine whether changes occur in these variables over time (i.e., after the intervention and at 3 and 12-months follow up). Exploratory correlational analyses will be conducted to examine associations between hormonal levels and other dependent variables. Subsequently, multiple linear regression analyses will be performed to determine which hormonal variables significantly predict subjective cognitive complaints, objective cognitive performance, and emotional variables, while controlling for relevant covariates (e.g., age and educational level).

Satisfaction with the intervention will be summarized using means and standard deviations derived from the satisfaction questionnaire. Additionally, adherence to the intervention will be calculated as the proportion of attended sessions relative to those scheduled.

Analyses will be conducted using the lme4 package (version lme4_1.1–13; [46]) in R statistical software (version 4.1.0; [47]) and SPSS v25.0 [48].

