The provision of the psychological intervention in an online group format constitutes also an innovative and cost-effective approach that will also help to overcome practical and clinical challenges found in long COVID-19 patients. Previous studies have indicated that long COVID-19 patients often report fatigue, muscle paint, general pain and joint pain [4] which may impede travelling to onsite healthcare centers to receive in-person attendance. Thus, online sessions will increase accessibility to psychological care in long COVID-19 populations. As for the group format of delivery it may facilitate peer support and shared learning experiences in health conditions [54]. On the other hand, many individuals with long COVID-19 often report feelings of loneliness, stigmatization and discrimination [55–58] and the group format may provide an opportunity to normalize and validate symptoms and to reduce social isolation. In fact, a recent systematic review indicated that people with long COVID-19 frequently use social media forums and online groups to connect with peers who have similar experiences [59]. Also importantly, the program has been designed considering the cognitive and physical limitations of long COVID-19 individuals, including scheduled breaks to help them to participate fully with the sessions. We expect that these patient-focused adaptations will help to facilitate engagement throughout the program, which should in turn contribute to high levels of satisfaction with the intervention. Taken together, these features not only improve accessibility and engagement but also have important clinical implications, as they provide a patient-centered model of psychological care that can be readily implemented in healthcare settings to address the emotional and social needs of long COVID-19 patients.

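### Repeated-measures ANOVA for the in-person tests and hair hormones drops anyone who misses a wave; if loss follows earlier scores, the estimated change is biased in a direction that cannot be known in advance

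*Protocol article*

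**What the plan says.** The protocol article assigns two methods to two groups of outcomes. For the questionnaire outcomes, Data analysis states that "Several linear mixed-effects models will be employed for each dependent variable to be analyzed", with a random intercept per participant. For the in-person outcomes in the experimental group (MoCA, Digit Symbol, Digit Span, hair cortisol and cortisone), the same section states that "Repeated measures ANOVAs with time as the within-subject factor will be performed to determine whether changes occur in these variables over time". No imputation or other handling of missing waves accompanies the ANOVA.

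The article describes the assessment times in two ways. Procedures has a first visit before treatment ("Participants in the experimental group will be required to complete an in-person additional assessment before they can begin the program") and then "At the three and twelve-month follow-up assessments, participants will repeat the in-person assessment to complete the neuropsychological and cognitive tests". Data analysis describes the pre-intervention status and then lists the times for change as "i.e., after the intervention and at 3 and 12-months follow up". Procedures schedules no in-person visit directly after the intervention.

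On missing data, the Participants section has "Considering an anticipated dropout rate of 20" per cent. The Discussion says that fatigue and pain are common in these patients, "which may impede travelling to onsite healthcare centers to receive in-person attendance", and that some participants may be reluctant to give hair. The last paragraph of the Control group section, which covers both groups, lets the team recommend discontinuation when symptoms worsen or when procedures, including hair sampling, are not followed.

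**The concern.** A standard repeated-measures ANOVA needs a full set of waves from each person. One missed visit or one unusable hair sample removes that person from every time point, so the 3-month change is estimated without those who later skip the 12-month visit. The article gives this method to the outcomes most exposed to missed visits, and gives a method that keeps partial records to the online questionnaires.

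The routes out of the data that the article names (symptom burden, worsening, non-adherence) may be related to the scores. A completer analysis is safe in general only if completers are a random subset. A likelihood analysis with a suitable covariance needs the weaker condition that missingness depends on observed data. At stake is the within-UP estimate of change itself, apart from the separate fact that these measures have no control group.

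**Working it through.** **The plan's own figures.** The article gives no sample size or power for the in-person outcomes. Its total of 74 belongs to the main comparison. That figure reproduces with the between-factors repeated-measures formula if the between-wave correlation is 0.5 (assumed, not stated): λ = 0.30² × 74 × 5 / (1 + 4 × 0.5) = 33.3 / 3 = 11.1, with 1 and 72 degrees of freedom, power 0.908. The inputs used here are 45 per arm and 20% dropout (Participants) and three in-person visits (Procedures).

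**Participants and records lost.**
- Completers: 45 × 0.80 = 36. If waiting-list participants who later receive the UP are included, 90 × 0.80 = 72.
- If all 9 dropouts leave after the 3-month visit, they leave 9 × 2 = 18 records out of 36 × 3 + 18 = 126, and the ANOVA discards 18/126 = 14.3%.
- If all 9 leave before the 3-month visit, they leave 9 records out of 117, and 9/117 = 7.7% is discarded.
- If instead each follow-up visit is missed independently at 20% (assumption), 45 × 0.80² = 28.8 are complete. Observed records are 45 × (1 + 2 × 0.80) = 117, of which 3 × 28.8 = 86.4 are used, so 26% is discarded. At 10% per visit, 36.5 are complete and 13% is discarded.

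**Bias.** Assumptions: three waves, unit SD, true change -0.30 SD at both follow-ups (negative means improvement), between-wave correlation 0.5 to 0.8, 20% missing at 12 months, and a logit slope of 1 to 1.5 per SD of the score that drives the loss, with poorer scores likelier to be lost.

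| Loss at 12 months driven by | Completers, 3-month change | Completers, 12-month change |
|---|---|---|
| Poor change by 3 months | -0.41 to -0.53 | -0.35 to -0.42 |
| Poor level at 3 months | -0.33 to -0.41 | about -0.30 |
| Baseline severity | -0.19 to -0.27 | -0.21 (correlation 0.5) and -0.26 (0.8) at slope 1 |

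Maximum likelihood with unstructured covariance stayed at about -0.30 in every row. A separate set-up, with higher scores better, a true 12-month change of +0.30 and dropout at either follow-up driven by earlier low scores, gave completer changes of 0.278 (moderate dependence) and 0.253 (stronger dependence). The likelihood estimate there was 0.299 to 0.301.

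**Precision under random loss.** There is no bias. For the 12-month change the standard errors were 0.163 (completers) and 0.159 (likelihood), and (0.163/0.159)² = 1.05, so about 5% in variance. For the 3-month change, with loss only at 12 months, completers use 36 people where 45 have both scores: 45/36 = 1.25, or 25%.

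**Which mixed model.** A random intercept forces equal correlations between all pairs of visits. If they are equal, it does as well as the unstructured model. With correlations of 0.7 between adjacent visits and 0.4 between first and last, and loss driven by 3-month change at slope 1.5, the random-intercept fit gave a 12-month change of -0.39. The unstructured fit gave -0.30.

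**The case against.** - **Listwise deletion is inferred.** The article names the test and not its missing-data rule, and an analysis plan that is not shown could add imputation. This is fair as far as it goes. But the method is a stated choice, deletion is what it does in standard software (including the general linear model procedure of SPSS, which the article names), and nothing stated prevents it.
- **Overstated benefit.** A reader might infer that completers would exaggerate the improvement. The documents do not support that direction. It follows if people who improved least stay away, but the article's own travel argument concerns how ill people are, and loss driven by baseline severity understates the change. A large loss of precision is not supported either for the 12-month change at the article's own dropout rate.
- **The set may exceed 45.** Procedures enrols waiting-list participants in the experimental group after 12 weeks under the same procedures, so up to 90 could contribute. This stands. It changes the counts and leaves the selection problem as it is.
- **Low stakes.** The Introduction calls this objective exploratory, without formal hypotheses, and it is single-arm. Participants agree beforehand to the assessment schedule and hair sampling, and receive reminders. All of this stands and limits severity. It is no reason to keep a less robust method when a better one costs almost nothing.

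**Conclusion.** The point holds with modest severity. The ANOVA would use about 36 of 45 participants (72 of 90) at the anticipated dropout. If missingness depends on earlier observed scores, the reported change can be off in either direction: about -0.19 to -0.53 SD at 3 months against a true -0.30 SD under the mechanisms tried. Those mechanisms, slopes and correlations are assumptions, and the article gives no basis for choosing among them. Under purely random loss the cost is precision only: about 5% in variance at 12 months and about 25% at 3 months. Data missing not at random would affect both methods.

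Two further inferences should be resisted. Reusing the random-intercept formula planned for the questionnaires is not sufficient, since it can stay biased when correlations between visits differ. Nor does any of this bear on the primary randomized comparison, which rests on other outcomes and another model.

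**What to change.** Replace the ANOVA sentence with a likelihood-based repeated-measures mixed model for each test score and hormone. Time enters as a categorical fixed effect, the within-person covariance is unstructured, and the model is fitted by REML to everyone with at least one in-person measurement. Report changes from pre-treatment with 95% confidence intervals, and keep the ANOVA as a sensitivity analysis. Three waves need 3 × 4 / 2 = 6 covariance parameters and four would need 4 × 5 / 2 = 10.

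Before the model's time points are fixed, reconcile Data analysis, which lists an assessment after the intervention, with Procedures, which places the in-person visits before the program and at 3 and 12 months. A further required wave would also increase listwise loss under the ANOVA. State whether waiting-list participants who later receive the UP enter this analysis.

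The cost is a few sentences and no new data. The mixed-model procedure in SPSS, already among the named software, fits this covariance; the random-intercept formula written for lme4 does not.

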#### Eligibility criteria and sample characteristics: Online videocall assessment.

Anxiety and Related Disorders Interview Schedule for DSM-5 (ADIS-5) [27]: this interview will serve to determine whether participants meet criteria for an emotional disorder. This interview allows us to assess major depressive disorder, dysthymia, panic disorder, agoraphobia, obsessive-compulsive disorder, generalized anxiety disorder, post-traumatic stress disorder, social anxiety disorder, hypochondria, and adjustment disorders. In our study, participants showing symptoms consistent with anxiety or depressive disorders “not otherwise specified” will also be considered for inclusion in the study.Sociodemographics: the research team has developed an *ad hoc* questionnaire to obtain sociodemographic data from participants. Thus, information about sex, age, place of residence, marital status, number of children, employment status, income, lifestyle habits (sleep, smoking, alcohol, physical activity, diet) will be collected at pre-treatment.Long COVID-19 questionnaire: participants will be asked about their COVID-19 and long COVID-19 history, including questions regarding the number and dates of COVID-19 infections, the number and dates of COVID-19 vaccine administrations, the date of long COVID-19 diagnosis, and physical symptoms related to COVID-19 (from their first infection and at the present).

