
#### Secondary study objective: Face-to-face assessment.

Montreal Cognitive Assessment (MoCA) [42]: this neurological test will be used to obtain a score of the overall level of cognitive abilities. It assesses several cognitive domains, including visuospatial skills, memory, working memory, attention, concentration, language, executive functions, and orientation. The maximum total score is 30 points. Scores between 26 and 30 may be interpreted as indicative of normal cognitive functioning, whereas scores of 25 or below suggests the presence of cognitive impairment.Digit Symbol subtest-Wechsler Adult Intelligence Scale-III (WAIS-III) [43]: this cognitive test assesses psychomotor speed, sustained attention, and incidental learning and is a paper-and-pencil subtest of the Wechsler Adult Intelligence Scale–III. Participants are required to match digits (1-9) with their corresponding symbols as quickly as possible within a 120-second time limit. The number of correctly matched symbols constitutes the matching score (maximum score = 133). Immediately afterwards, incidental learning is assessed through an untimed cued-recall task (maximum score = 18) and an untimed free-recall task without digit cues (maximum score = 9).Digit subtest from Wechsler Adult Intelligence Scale-IV (WAIS-IV) [44]: this subtest assesses verbal short-term and working memory, and it is administered orally. In the Digit Span Forward task, participants must repeat sequences of numbers in the same order, which provides an indication of their verbal short-term memory. In the Digit Span Backward task, participants reproduce number sequences in reverse order to assess verbal working memory. Memory capacity is defined as the maximum span length, which is the longest sequence that can be correctly recalled. The maximum span is 9 for the Digit Span Forward task and 8 for the Digit Span Backward task. Two trials are administered at each sequence length. Additionally, performance can be expressed as a raw score, which is calculated by adding together the number of sequences correctly recalled, with a maximum raw score of 16 for both tasks. Higher scores indicate better verbal short-term and working memory performance.Cortisol and cortisone: hair samples will be collected from the posterior vertex or nape area, where hair growth is continuous and less exposed to external contaminants. This sampling site is recommended due to its lower intra-individual variability and greater representativeness of long-term systemic hormone exposure. A small section of hair will be tied with thread near the cut end to identify the portion closest to the scalp during analysis and to prevent hair loss. Using clean scissors, the hair will be cut as close as possible to the scalp, obtaining a segment approximately 3 cm in length. This length allows for the assessment of cortisol and cortisone levels accumulated over the past three months, based on an average hair growth rate of 1 cm per month.

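### The exploratory neuropsychological and hair analysis names a post-intervention occasion for which the text describes no in-person collection, and uses a repeated-measures ANOVA that usually drops anyone with a missed visit

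*Protocol article*

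**What the plan says.** The Data analysis section assigns repeated-measures ANOVA, with time as the within-subject factor, to the neuropsychological tests and to hair cortisol and cortisone in the experimental group. It defines the occasions as "i.e., after the intervention and at 3 and 12-months follow up", in addition to the description before therapy.

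The Procedures section gives the collection schedule:

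- Before therapy: "Participants in the experimental group will be required to complete an in-person additional assessment before they can begin the program". This visit includes the tests and a hair sample.
- After therapy: "After the intervention, participants will complete the online post-treatment assessment protocol, which will include the measures administered at pre-treatment and a satisfaction questionnaire".
- Later: "At the three and twelve-month follow-up assessments, participants will repeat the in-person assessment to complete the neuropsychological and cognitive tests", again with hair.

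The Outcomes section classes these tests and the hair sample as face-to-face measures. Of the 3 cm hair segment it says: "This length allows for the assessment of cortisol and cortisone levels accumulated over the past three months".

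The regressions that follow the ANOVA relate hormone levels to cognition and emotion "while controlling for relevant covariates (e.g., age and educational level"). The sociodemographic questionnaire is described as collecting "information about sex, age, place of residence, marital status, number of children, employment status, income, lifestyle habits", the last of these followed by examples in brackets. Education is not in the list.

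**The concern.** An analysis can use only the occasions at which the measure is taken. If the text is right that the assessment directly after therapy is an online protocol, there is no cognitive test score or hair sample for the first of the three follow-up occasions that the ANOVA names. A model with that occasion as a level of the time factor could not be fitted, and an immediate change after therapy could not be estimated.

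For hair the question is also what a value means. Each sample looks back over about three months, so the sampling date decides whether it reflects the period before, during or after therapy. The Introduction wants these measures as possible physiological correlates of the intervention, so the reader must know which period each one covers.

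Two smaller matters lie in the same paragraph. Repeated-measures ANOVA handles missed visits poorly, and missed visits are foreseeable: the plan allows for 20% dropout, and the Discussion expects some reluctance to give hair. A covariate named for the regressions also does not appear among the items collected.

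**Working it through.** **Occasions, side by side**

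| Occasion | In-person tests and hair (Procedures) | Tested (Data analysis) |
|---|---|---|
| Before the program | yes | yes, as baseline |
| Post-treatment | online assessment; none described | yes |
| 3 months | yes | yes |
| 6 months | online assessment; none described | no |
| 12 months | yes | yes |

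Collection describes 3 occasions and the analysis names 4. The analysis leaves out 6 months, in line with the schedule; post-treatment is the only row where the two sections differ. The statement that the post-treatment protocol repeats the pre-treatment measures does not close the gap. The online pre-treatment protocol is completed before allocation, whereas the in-person visit is a separate, additional assessment for the experimental group.

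**Period covered by each hair sample**

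Inputs: a 3 cm segment at 1 cm per month gives 3 / 1 = 3 months (Outcomes); therapy takes 12 weeks (Control group section), and 12 × 12/52 ≈ 2.8 months; follow-ups count from the end of therapy (Procedures). With month 0 as the start of therapy:

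- Baseline sample, about month 0: covers months −3 to 0, before therapy.
- 3-month sample, about month 2.8 + 3 = 5.8: covers months 2.8 to 5.8, after therapy.
- 12-month sample, about month 2.8 + 12 = 14.8: covers months 11.8 to 14.8.
- A post-treatment sample, if one is taken, at about month 2.8: would cover months −0.2 to 2.8, which is the therapy period.

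On the schedule in the text, no sample covers months 0 to 2.8. The growth rate is an average, so the limits are approximate; in a slow grower the 3-month sample would reach back into the last part of therapy.

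**Effect of dropping incomplete participants**

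The plan gives no sample size for this analysis to reproduce; its figure of 74, raised to 90, is for two conditions and five assessments. Taking its 45 per arm and 20% dropout as given:

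- Complete participants: 45 × (1 − 0.20) = 36, so 9 are dropped.
- With 3 occasions the ANOVA uses 36 × 3 = 108 observations. If all 9 attended baseline, all available data would be 108 + 9 = 117 observations if they leave before the 3-month visit, and 108 + 18 = 126 if they leave after it.
- If instead 5% to 20% are lost at each of the two repeat visits (an assumption), 45 × 0.95² = 40.6 to 45 × 0.80² = 28.8 remain complete.
- Detectable within-group effect at 80% power and alpha 0.05, with 3 occasions, from the noncentral F with λ = f² × n × m / (1 − ρ) and degrees of freedom m − 1 and (n − 1)(m − 1). The correlation ρ = 0.5 is assumed, because the protocol gives none. Result: f = 0.19 at n = 45 and f = 0.22 at n = 36.

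**Education**

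The covariate is named in Data analysis. The listed items are sex, age, residence, marital status, children, employment, income and lifestyle habits. Age is there; education is not.

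**The case against.** The strongest objection is that the Outcomes section sends the reader to Fig 1 for the measures and format at each time point, and Fig 1 could not be read here. It may show a post-treatment in-person visit. The Procedures section calls the post-treatment protocol online but does not say that nothing else happens then. A reader might infer that no post-treatment tests or hair exist; the documents do not establish that. What stands is that the two sections differ as printed, and one of them needs correcting whatever the figure shows.

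On the ANOVA, a reader might infer that the plan prescribes a complete-case analysis. It does not: it states no missing-data rule, and such rules are commonly left to the analysis plan. The method is stated, however, and its usual form drops incomplete participants. The figure of 36 of 45 is only an illustration, because it applies a trial-wide dropout allowance to one arm. Waiting-list participants later follow the same procedures, so more than 45 may contribute. Nor can one say that nine participants' 3-month data would be lost, since that needs all nine to leave after that visit.

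On education, a reader might infer that it is not collected. It is only an example covariate, and the article may condense the questionnaire. This supports a check and no more.

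Finally, the Introduction calls this objective exploratory and proposes no formal hypotheses for it. The plan makes no claim about cortisol during therapy, so the hair point is a caution about interpretation and not an error already made.

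**Conclusion.** The inconsistency is real: the analysis names a post-intervention occasion for measures that the text collects only before the program and at 3 and 12 months. If Procedures is right, the ANOVA cannot be run with the occasions stated, and the hair results say nothing direct about the 12 therapy weeks. If Data analysis is right, Procedures omits a visit. This rests on the text alone, with Fig 1 unseen.

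The choice of ANOVA is a secondary weakness of moderate size. Retaining 36 of 45 raises the detectable effect from f = 0.19 to f = 0.22 under the assumed correlation. Dropping incomplete participants can also bias the result if loss depends on earlier scores. Education is a point to verify. None of this affects the comparison of the UP with the waiting list on the primary outcomes.

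**What to change.** 1. Reconcile Procedures, Data analysis and Fig 1 so that collection and analysis name the same occasions. If a post-treatment in-person visit exists, add it to Procedures and keep four occasions. If it does not, analyse pre-treatment, 3 and 12 months.
2. In the latter case, state that the 3-month hair sample reflects roughly the three months after therapy, and make no claim about cortisol or cortisone during therapy.
3. Replace the repeated-measures ANOVA with the linear mixed model already planned for the questionnaires, with time as a categorical fixed effect and a random intercept per participant, fitted to all available data. State whether waiting-list participants who later receive the UP are included.
4. Check the ad hoc questionnaire for educational level. If it is missing, add the item and ask participants already enrolled once, online.

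The cost is a change of wording, a model the team already plans to fit, and at most one questionnaire item. If the schedule in Procedures is right, no visit or sample is added.
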